### Sample Size

Sample size and statistical power were calculated for the primary outcome measure using G*Power 3.1.9.2 [20]. Detecting a 2-point difference (effect size of 0.44) between the 2 groups on HADS with an alpha of .05 and 80% power requires 81 participants in each group for a total sample size of 162 participants. Given the discharge rate of 80 patients per month and a recruitment rate of 30%, it is estimated that it will take 7 months to recruit the required sample size.

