**Methods:**

In total, 162 patients that survived an ICU experience will be recruited and randomized into 1 of 2 groups. The intervention group will receive access to the Web-based intensive care recovery program, ICUTogether, 2 weeks after discharge (n=81), and the control group will receive usual care (n=81). Mental well-being will be measured using the Hospital Anxiety and Depression Scale, The Impact of Events Scale-Revised and the 5-level 5-dimension EuroQoL at 3 time points (2 weeks, 6 months, and 12 months post discharge). Family support will be measured using the Multidimensional Scale of Perceived Social Support at 3 time points. Analysis will be conducted on an intention-to-treat basis using regression modeling. Covariates will include baseline outcome measures, study allocation (intervention or control), age, gender, length of ICU stay, APACHE III score, level of family support, and hospital readmissions. Participants’ evaluation of the mobile website will be sought at 12 months postdischarge. A cost utility analysis conducted at 12 months from a societal perspective will consider costs incurred by individuals as well as health care providers.

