### Data Collection and Measures

Following the consent process, demographic data will be collected from the participants’ health records, which will include the age, gender, admission diagnosis, severity of illness (APACHE III), existing comorbidities, and ICU length of stay. Data will be collected from participants at the following 3 time points: 2 weeks post discharge, 6 months post discharge, and 12 months post discharge (primary timepoint). The following three outcome measures will be used in the study: the Hospital Anxiety and Depression Scale (HADS), the Impact of Events Scale Revised, and the 5-level 5-dimension EuroQoL. All 3 measures will be completed at each of the 3 time points. The level of family support will also be collected at these time points via the Multidimensional Scale of Perceived Support [14]. Table 1 provides a brief description of each of the outcome measures. Participants in both groups will receive the 3 surveys by email 2 weeks post discharge from the hospital to complete the first data collection time point. At the following 2 data collection time points, the 3 surveys will be sent by via email to both groups. All participants will also be contacted by telephone to provide a prompt to complete the surveys at the data collection time points.

**Table 1 table1:** Summary of outcome measures and description.

Outcome measure		Number of items	Description

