### Statistical Analysis

Data will be reported in accordance with the Consolidated Standards of Reporting Trial. Data analysis will be conducted using SPSS version 24 (IBM) and Stata SE version 15 (StataCorp). The characteristics of participants in each arm of the study will be summarized using descriptive statistics. Analysis of characteristics to determine similarity between the arms will be conducted using chi-square tests for categorical data and independent *t* tests for continuous data.

Further analysis will include stratifying the APACHE III scores into categories to determine if there is a difference in the level of severity and outcomes. The 3 outcome measures (HADS, IES, and QoL) at follow-up will be analyzed as dependent variables using regression modeling. Covariates will include baseline outcome measures, study allocation (intervention or control), age, gender, length of ICU stay, APACHE III score, and level of family support. Analysis will be conducted on an intention-to-treat basis. A subanalysis of the intervention group based on those who engaged with the mobile website compared with those who did not will also be conducted. The characteristics of people who withdraw from the study will be compared with those who remain in the study. Missing data will be addressed using multiple imputation assuming variables are missing at random. The person who completes the data analysis will be blind to participant allocation status. Summary statistics of frequency of use, time spent using the site, most frequently used elements, and time spent on each screen will be reported.

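### The 162 patients to be randomized are exactly the complete-data requirement of an unadjusted comparison, so the stated 80% power allows for no loss by 12 months

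*Protocol article*

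**What the plan says.** The Sample Size section starts from "Detecting a 2-point difference (effect size of 0.44) between the 2 groups on HADS", "with an alpha of .05 and 80% power", and concludes that this "requires 81 participants in each group for a total sample size of 162 participants". It then estimates the recruitment time for that same number.

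The abstract (Methods) sets the number to be enrolled: "In total, 162 patients that survived an ICU experience will be recruited and randomized into 1 of 2 groups". Both arms are given as 81; for the comparator, "the control group will receive usual care (n=81").

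Data Collection and Measures places the main comparison at "12 months post discharge (primary timepoint"). HADS is also collected at 2 weeks and 6 months.

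Statistical Analysis plans an intention-to-treat regression that includes the baseline outcome measure among its covariates, with multiple imputation under missing at random. It adds that "The characteristics of people who withdraw from the study will be compared with those who remain in the study". No section gives an expected loss rate, an inflation of the sample size, or a correlation between baseline and 12-month HADS.

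**The concern.** The number required and the number randomized are both printed, and they are equal. If 81 per arm is the number needed with 12-month data, randomizing 81 per arm meets it only when everyone is followed. The outcome is a self-completed survey one year after hospital discharge in survivors of critical illness, and the plan makes provision for people who withdraw.

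The calculation also does not describe the planned analysis. It is a plain two-group comparison, whereas the outcome will be analysed by regression adjusted for baseline. Loss lowers power and baseline adjustment raises it, and the stated 80% reflects neither.

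What is at stake is how the result is read. The article says that the findings will inform a larger study. If the comparison is null, readers will judge it against 80% power, and that figure was not worked out for the number of patients or the model that will produce the result.

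**Working it through.** **Inputs from the article.** Difference 2 points; effect size d = 0.44, hence an implied SD of 2/0.44 = 4.55 (2/4.5 = 0.444 also rounds to 0.44); alpha 0.05, sidedness not stated; power 80%; 81 per arm.

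**Inputs assumed, because the article gives none.** Loss of 10% to 40% by 12 months, equal in the two arms; baseline to 12-month correlation r of 0.3 or 0.5.

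**Step 1: reproduce the 81.** For a two-sided t test with n per arm, the noncentrality is d × √(n/2) on 2n − 2 degrees of freedom.

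- n = 81, d = 0.44: noncentrality 0.44 × √40.5 = 2.80, critical t 1.975, power 79.5%.
- n = 81, d = 0.444: power 80.3%, and 81 is the smallest n that reaches 80%.
- One-sided, d = 0.44: 65 per arm would suffice (64 by the normal approximation), which does not match 81.

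So 81 is the two-sided, complete-data requirement, and no allowance for loss is hidden in it.

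**Step 2: apply loss to the unadjusted calculation.** Put n = 81 × (1 − loss) into the same formula with d = 0.44. At 20% loss, n = 64.8, noncentrality 0.44 × √32.4 = 2.50, power 70.0%.

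**Step 3: add the planned baseline adjustment.** Adjustment reduces the residual SD by the factor √(1 − r²), so d becomes d/√(1 − r²): 0.44/√0.91 = 0.461 for r = 0.3, and 0.44/√0.75 = 0.508 for r = 0.5.

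| Loss | n per arm with data | Power, unadjusted | Power, r = 0.3 | Power, r = 0.5 | Difference detectable at 80% power, unadjusted (SD 4.55) |
|---|---|---|---|---|---|
| 0% | 81 | 79.5% | 83.1% | 89.5% | 2.01 |
| 10% | 72.9 | 75.1% | 79.0% | 86.1% | 2.12 |
| 20% | 64.8 | 70.0% | 74.1% | 81.9% | 2.25 |
| 30% | 56.7 | 64.2% | 68.3% | 76.5% | 2.41 |
| 40% | 48.6 | 57.4% | 61.4% | 69.8% | 2.61 |

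Using d = 0.444 instead raises the power figures by up to about one percentage point and changes nothing in substance.

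**Step 4: the break-even correlation.** Solving for the r that brings adjusted power back to 80% gives about 0.34 at 10% loss, 0.46 at 20%, 0.56 at 30% and 0.64 at 40%.

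**Limit of these figures.** They count a patient without a 12-month score as contributing nothing. Imputation that uses the 6-month score would do somewhat better than that.

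**The case against.** The strongest reply is that the planned analysis is not an unadjusted t test. With r = 0.5 the adjusted regression still has about 82% power at 20% loss, and multiple imputation can draw on the 6-month HADS of patients who miss the 12-month survey. On that view the trial may have its 80% after all.

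Most of this stands, and it limits what can be said. A reader might infer that the 80% holds only if nobody is lost, or that the design does not have 80% power. The documents do not support either inference: over the assumed range, the planned model lies on both sides of 80%. A reader might also infer that imputation contributes nothing. It may recover some of the lost information, though in general not all.

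Three further inferences should be avoided. The 81 is not an arithmetic error, since it reproduces. The plan does not forecast a rate of withdrawal; it only says how withdrawals and missing data will be handled. And the article does not say which HADS score the 2 points refer to, but an article may leave such detail to the full protocol, so it adds no weight here.

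What the reply does not do is rescue the statement as written. The Sample Size section uses no correlation, so it cannot be taken to have traded baseline adjustment against loss. Condensation into an article is no answer either, because both the required and the randomized number are printed. The gain from adjustment also depends on a baseline HADS that is itself collected 2 weeks after discharge, after randomization, so some patients could lack both scores.

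**Conclusion.** The point holds in this form: the stated 80% belongs to an unadjusted comparison with all 162 patients measured at 12 months, and it makes no allowance for loss. On that calculation power is about 75%, 70%, 64% and 57% at 10%, 20%, 30% and 40% loss. Under the planned baseline-adjusted model it is about 86%, 82%, 76.5% and 70% with r = 0.5, and about 79%, 74%, 68% and 61% with r = 0.3.

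The equality of the two numbers and the absence of a margin are facts of the document. The size of the effect on power rests on assumed loss rates and correlations, equal loss in the arms, and no contribution from patients without a 12-month score. The true power of the planned analysis could be above or below 80%. The plan gives no basis for saying which, and it prints 80% all the same. There is no issue of bias or type I error here.

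**What to change.** Keep 162 and rewrite the power statement in the Sample Size section for the planned regression. State:

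- the number of patients expected to have 12-month HADS, with the assumed loss rate and its basis;
- the assumed correlation between baseline and 12-month HADS, with its basis;
- the resulting power for 2 points, and the difference detectable with 80% power.

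For example: with 30% loss and r = 0.5, about 57 per arm have 12-month data, power for a 2-point difference is about 76.5%, and the difference detectable with 80% power is 2.41 × √0.75 = 2.09 points. A small table over two or three loss rates and correlations would serve if neither value can be fixed with confidence.

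The cost is a few sentences, with no extra patients and no change to the analysis. The downside is that the stated power may become less favourable.

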### Statistical Analysis

Data will be reported in accordance with the Consolidated Standards of Reporting Trial. Data analysis will be conducted using SPSS version 24 (IBM) and Stata SE version 15 (StataCorp). The characteristics of participants in each arm of the study will be summarized using descriptive statistics. Analysis of characteristics to determine similarity between the arms will be conducted using chi-square tests for categorical data and independent *t* tests for continuous data.

Further analysis will include stratifying the APACHE III scores into categories to determine if there is a difference in the level of severity and outcomes. The 3 outcome measures (HADS, IES, and QoL) at follow-up will be analyzed as dependent variables using regression modeling. Covariates will include baseline outcome measures, study allocation (intervention or control), age, gender, length of ICU stay, APACHE III score, and level of family support. Analysis will be conducted on an intention-to-treat basis. A subanalysis of the intervention group based on those who engaged with the mobile website compared with those who did not will also be conducted. The characteristics of people who withdraw from the study will be compared with those who remain in the study. Missing data will be addressed using multiple imputation assuming variables are missing at random. The person who completes the data analysis will be blind to participant allocation status. Summary statistics of frequency of use, time spent using the site, most frequently used elements, and time spent on each screen will be reported.

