### Randomization

Permuted block randomization will be conducted in blocks of 20 using a computer random number generator. Allocation concealment will be conducted by an independent researcher using sequentially numbered, opaque, sealed envelopes. The independent researcher will provide the researcher conducting the consent process with the sequentially numbered, sealed, opaque envelopes. Envelopes containing the treatment allocation will only be opened by the recruiting researcher on participant enrollment. Blinding of the participant to allocation status will not be possible owing to the nature of the intervention. The researchers conducting the data analysis will be blinded.

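### The severity analysis cuts APACHE III into categories although the score is already a model covariate, which costs information and power in a further analysis whose question is not made clear

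*Protocol article*

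**What the plan says.** The severity analysis is one sentence in Statistical Analysis. It describes further analysis by "stratifying the APACHE III scores into categories to determine if there is a difference in the level of severity and outcomes".

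The next sentences set out the main models: "The 3 outcome measures (HADS, IES, and QoL) at follow-up will be analyzed as dependent variables using regression modeling". The covariates are the baseline measures, allocation, and "age, gender, length of ICU stay, APACHE III score, and level of family support". Data Collection and Measures has APACHE III taken from each participant's health record. No allocation-by-severity term is listed.

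The number of categories, the cut-points and the test are not given. A condensed article may leave these to the full protocol or the statistical analysis plan, so their absence is not part of this point. The point concerns the method that is stated, which is categorisation.

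**The concern.** APACHE III is a numerical score, and the covariate list treats it as one. The one analysis devoted to severity nevertheless replaces it with bands. Banding treats everyone within a band as equally ill, makes the answer depend on the cut-points and, if the relation is roughly linear, lowers power. With 162 participants there is little power to spare.

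The sentence can also be read in two ways. It may ask whether outcome varies with severity (prognosis), or whether the programme's effect varies with severity (effect modification). The second question needs an allocation-by-severity term, and none is named. The article says its findings will inform a larger study, so a severity result, even an exploratory one, should be estimated in the way that best uses the data.

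**Working it through.** **Inputs.** From Sample Size: "Detecting a 2-point difference (effect size of 0.44) between the 2 groups on HADS", "with an alpha of .05 and 80% power", and it "requires 81 participants in each group for a total sample size of 162 participants". Assumed, because the article does not give them: APACHE III roughly normal, a linear relation, 2 to 4 equal-sized groups, two-sided tests at 0.05, and all 162 participants contributing.

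**The plan's own figure.** The implied SD is 2/0.44 = 4.55 HADS points. The normal formula gives n per arm = 2 × ((1.96 + 0.84)/0.44)² = 81.08, or 82 rounded up. The exact t calculation gives 83 for an effect size of 0.44, and 81 for 0.444, which rounds to 0.44. The stated 81 is reproduced to within 2 per arm. It is used here only for the SD and the total.

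**Information kept.** For a standard normal score cut into k equal groups, the share of linear information kept is R = the mean of the squared group means.

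- k = 2: group means ±0.798, R = 0.64
- k = 3: group means ±1.091 and 0, R = 0.79
- k = 4: group means ±1.271 and ±0.325, R = 0.86

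**Prognostic reading.** Take a true correlation r = 0.22, chosen because the continuous score then has about 80% power. The noncentrality is λ = N r²R/(1 − r²R), with R = 1 for the score itself.

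| Form of APACHE III | λ | Power, omnibus test | Power, trend test |
|---|---|---|---|
| Continuous | 162 × 0.0484/0.9516 = 8.24 | 81% (1 df) | – |
| 2 groups | 5.15 | 62% | 62% |
| 3 groups | 6.47 | 61% | 71% |
| 4 groups | 7.04 | 58% | 75% |

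The λ column is for the omnibus test. Adding groups does not restore omnibus power, because the extra degrees of freedom offset the information regained. A trend test across groups recovers part of the loss.

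**Effect-modification reading.** Let the treatment effect change by b HADS points per SD of APACHE III.

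- Continuous term: SE = 2 × 4.55/√162 = 0.714. Power = Φ(b/0.714 − 1.96).
- Median split: the contrast between halves is 2 × 0.798 × b, with SE = 4.55 × √(4/40.5) = 1.43. Power = Φ(1.596b/1.43 − 1.96).

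| b (points per SD) | Continuous | Median split |
|---|---|---|
| 1.0 | 29% | 20% |
| 1.5 | 56% | 39% |
| 2.0 | 80% | 61% |

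Eighty per cent power on the continuous term needs b = 2.80 × 0.714 = 2.0 points per SD. The effect would have to change by the whole planned treatment difference for each SD of severity.

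**The case against.** The strongest reply is that the planned regressions already contain the APACHE III score. If it enters as a number, they already give a severity-outcome slope, and the banded analysis is an addition. That is right, and it makes the prognostic part of the fix a matter of reporting a term already in the model. That the covariate is continuous is an inference from the word score, though a natural one.

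A reader might infer that the plan tests treatment within each severity stratum and so cannot show a real difference by severity. The document does not support this. The sentence mentions neither arms nor tests within strata, and on the prognostic reading categories can show a difference, only with less power. Figures for that hypothetical plan illustrate a risk to avoid and do not measure the stated analysis. With tertiles of 27 per arm and the planned effect in all three, each test has about 35% power, and the chance of a mix of significant and non-significant strata is 1 − 0.355³ − 0.645³ = 69%. What stands is the general rule: if strata were compared in that way, differing significance would not show effect modification.

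It is also fair that the power losses rest on assumptions. With a threshold or non-monotone relation, bands could do better than a straight line, which is why a spline is offered. And a continuous interaction term would not make modest effect modification detectable: at 1 point per SD both forms are underpowered.

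**Conclusion.** The point holds as a small improvement to an exploratory analysis. Whichever question is meant, banding APACHE III is a weaker method than using the score that the trial collects and already lists in its models. Under a normal score, a linear relation and 2 to 4 equal groups, the loss is about 14% to 36% of the information. Power falls from about 80% to about 60% with an omnibus test, or to 62% to 75% with a trend test. Missing outcomes would lower all these power figures.

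If effect modification is the question, the stated plan also lacks the term that would estimate it. The document does not show that strata will be misread, or that severity results will steer the larger study.

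**What to change.** State in Statistical Analysis which question is meant, and replace the categorisation accordingly:

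- **Prognosis:** report the continuous APACHE III term, linear or as a restricted cubic spline, from the planned regressions.
- **Effect modification:** add one allocation × continuous APACHE III term to the 12-month HADS regression. Report its estimate and 95% CI as exploratory, and note that 162 participants can detect only large modification.
- **Categories:** use them for display only, for example model-based estimates at chosen percentiles of the score, with no tests within categories.

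The cost is a sentence or two of text and at most one model term, with no new data. The presentation is slightly less simple than a table by category, and a spline spends an extra degree of freedom or more compared with a straight line.

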### Economic Outcomes

A cost utility analysis will be conducted at 12 months to determine whether the Web-based recovery program is a cost-effective approach for improving the quality of life of ICU survivors when compared with usual care. The perspective taken for the economic analysis will be a societal perspective and will include costs incurred by individuals as well as health care providers.

#### Identification of Costs and Benefits

The primary outcome measure for assessing benefits will be quality of life. The identification of costs will be across the following 4 main areas:

*Intervention costs* include ongoing mobile website maintenance such as hosting costs as well as the cost of promoting the mobile website to future ICU survivors. The cost for developing the mobile website and implementing the intervention for the study will not be included because these costs will not be incurred in future implementation of the mobile website.*Health care costs* include GP visits; other health practitioner consultations such as counseling services, dieticians, and physiotherapists; emergency department visits; hospital inpatient stays in acute or mental health settings; mental health outpatient visits; and medication use.*Personal and family costs* include the use of alternative therapies such as massage and reflexology, as well as the use of health promotion resources such as sporting facilities and support groups. Travel costs to attend health services and health promotion activities will also be included. The time cost for using the mobile website will not be included as this will occur during leisure time and is expected to be minimal.*Productivity costs* include time spent absent from work owing to illness.

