### Intervention

Patients in the intervention group will receive access to a Web-based recovery program, ICUTogether that is accessible via smart devices and personal computers. The mobile website will provide information about health and well-being during recovery, including advice about exercise, sleep, and nutrition. Information will be provided on the recovery process, the signs and symptoms of potential complications during recovery, and when and how participants should seek professional help. Participants will be encouraged to keep a journal to promote reflection on progress over time and to explore their thoughts and feelings during their recovery. A chat room will also be available and participants will be able to post items to share with other participants in the study.

Participants will be given access to the mobile website 2 weeks following discharge from the hospital. A hard copy the self-help guide and telephone call will guide participants regarding the use of the site. If the participant is still unable to use the website, a researcher will visit their home and provide direct support with it. A demonstration of the functionality of the mobile website by a researcher will also be given at that time. The frequency of use of the website is at the discretion of the participants who will be encouraged to use the site as frequently as they wish. Each time a participant logs in, they will be prompted to complete a symptom checker that will identify material most useful to the participant at that point in time. The score from the symptom checker will be monitored and an alert notification will be sent to the researchers when the scores reach a certain level and thus gives cause for concern. Participants will receive a weekly email summarizing their participation over the previous 7 days and indicating any days they have not participated along with a prompt to continue participating.

The mobile website was developed by an external provider in collaboration with the researchers. The mobile website is being tested for ease of use and navigation properties by the researchers, clinicians, and a group of ICU survivors prior to commencement of the study.

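### The cost-utility analysis leaves out the staff support that belongs to the tested intervention, so the incremental cost of what was delivered is understated

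*Protocol article*

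**What the plan says.** **What is costed.** Under Identification of Costs and Benefits, the protocol article says that intervention costs "include ongoing mobile website maintenance such as hosting costs as well as the cost of promoting the mobile website to future ICU survivors". It then states that "The cost for developing the mobile website and implementing the intervention for the study will not be included", and gives the reason: "because these costs will not be incurred in future implementation of the mobile website".

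**How it is measured and valued.** The two sections that follow obtain intervention costs from the website developers, from a promotion plan still to be written, and from the average of three service-provider quotes. No record of researcher time is described.

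**What is delivered.** The Intervention section includes these elements:
- Printed material and a call, described thus: "A hard copy the self-help guide and telephone call will guide participants regarding the use of the site".
- Home support for anyone whom this does not get onto the site, in that "a researcher will visit their home and provide direct support with it".
- A researcher's walk-through of how the site works, apparently on the same occasion.
- Symptom-checker scores are monitored, and "an alert notification will be sent to the researchers when the scores reach a certain level".

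**What controls receive.** The Control Group section limits contact to consent and surveys. Data Collection and Measures adds telephone reminders about the surveys, but these go to both arms.

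**How cost and effect are combined.** QALYs come from the trial's own EQ-5D data. The ICER is the between-arm cost difference divided by the between-arm QALY difference. The stated perspective is societal and includes provider costs.

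**The concern.** A cost-utility ratio is interpretable only if its numerator and denominator describe the same intervention. Here the QALYs come from participants who had the website plus human support, while the costing rule prices the website plus promotion. The reason given for the exclusion fits development, which is paid once. It fits poorly with items that arise again with each new user, such as a guide, a call, a visit or the handling of an alert.

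Cost-effectiveness is part of the article's stated objective, and the findings are meant to inform a larger study. A cost figure that omits delivery would carry forward into that planning. Recruitment is already under way, and staff time not logged as it happens is hard to recover later.

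**Working it through.** The protocol states no incremental cost, staff time or ICER, so there is no figure of its own to reproduce. The check has three steps.

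**1. Match each delivered element to a cost source.**

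| Element (Intervention section) | Arm | Named among intervention costs? | Measurement route? |
|---|---|---|---|
| Printed guide | Intervention only | No | None described |
| Telephone call on using the site | Intervention only | No | None described |
| Home visit with demonstration, if still unable to use the site | Intervention only, some participants | No | None described |
| Monitoring of scores and alerts | Intervention only | No | None described |
| Hosting and maintenance | Intervention only | Yes | Developers, provider quotes |
| Promotion | Future users | Yes | Promotion plan, provider quotes |
| Survey reminder calls | Both | Not relevant | Cancel in the difference |

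The health care cost category does not rescue the first four rows. It lists GP, allied health, emergency, inpatient, outpatient and medication use, not researcher contact.

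**2. Direction.** Let c > 0 be the mean cost of the support per intervention participant, ΔC the cost difference as planned, and ΔQ the QALY difference.

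- Incremental cost as delivered = ΔC + c. The planned figure is too low by c, whatever the sign of ΔQ.
- ICER as delivered = (ΔC + c)/ΔQ = ΔC/ΔQ + c/ΔQ. If ΔQ > 0, the planned ICER is too low by c/ΔQ. If ΔQ is zero or negative, that statement does not hold.
- Net monetary benefit at willingness to pay λ = λΔQ − ΔC. The planned value is too high by c at every λ, so the planned acceptability curves are affected as well.

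The result has the same structure whichever way roll-out goes. If roll-out keeps the support, c is a real cost that is missing. If roll-out drops it, c is rightly zero, but ΔQ was not observed for that version.

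**3. Size, on assumed inputs only.** The documents give neither c nor ΔQ. The hours, rates and QALY gains below are assumptions, and travel and printing are left out.

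- Low: 0.5 h call + 2 h visit × 10% of participants + 0 h monitoring = 0.7 h. At Aus $40 per hour, c = Aus $28.
- Middle: 0.5 + 2 × 30% + 1 = 2.1 h. At Aus $60, c = Aus $126.
- High: 1 + 3 × 50% + 3 = 5.5 h. At Aus $80, c = Aus $440.

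| c | c/ΔQ at ΔQ = 0.05 | at 0.02 | at 0.01 |
|---|---|---|---|
| Aus $28 | 560 | 1,400 | 2,800 |
| Aus $126 | 2,520 | 6,300 | 12,600 |
| Aus $440 | 8,800 | 22,000 | 44,000 |

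The entries (Aus $ per QALY) run from 560 to 44,000, a ratio of about 79 (44,000/560). That spread shows that the amount could be trivial or material. It is not an estimate.

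**The case against.** The best defence is that this is a disclosed choice. The plan costs future implementation rather than trial delivery, and says why. The excluded item is qualified as belonging to the study, which could mean trial-specific set-up. None of the guide, call, visit or alert handling is named as excluded. The list of intervention costs is not expressly closed, and the promotion plan might pick up a printed guide. The support mostly helps people to get onto the site, and nothing shows that it drives the QALY difference. Visits go only to those who cannot manage otherwise, and the demonstration appears to be tied to the visit. The text does not say what staff do, or for how long, when an alert arrives.

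Much of this stands. The exclusion of each staff item is an inference from the wording and from the missing measurement route. The demonstration should not be counted as a separate cost for everyone. Costing for roll-out is legitimate if it is labelled as such.

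What does not stand is the idea that the choice removes the mismatch. The support is described under the intervention itself and is given to one arm only. The plan neither states nor tests the assumption that the effect would survive without it. The sensitivity analysis names health provider, individual and productivity costs and takes its distributions from the data. Staff time that was never recorded cannot enter that way.

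A reader might go further and infer that the ICER is certainly biased in the website's favour, or by a decisive amount, or that the analysis evaluates an entirely different product. The documents do not support this. The ICER statement needs a positive QALY difference, the amount is unknown, and the web content is not shown to differ between the trial and roll-out.

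**Conclusion.** The point holds in limited form. Applied as written, the plan understates the incremental cost of the intervention as delivered by the cost of its staff support. It understates the ICER as well if the QALY difference is positive. The conclusion rests on reading the excluded implementation cost as covering this support, a reading backed by the absence of any staff-time source. The size cannot be computed from the documents and may be small. Leaving out one-off development cost is defensible. The HADS analysis is not affected, so this is a correction that should be made to the economic evaluation and not a threat to the trial's primary result.

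**What to change.** - Keep a short log for the intervention arm: researcher minutes on calls, visits (with any demonstration) and alert handling, plus travel and printed materials. For participants already supported, use whatever records exist and mark the values as estimates.
- Value these items in Aus $ 2018, as for the other costs. The per-kilometre method already in the plan can serve for car travel. Include them as recurrent delivery costs in the base case and in the probabilistic sensitivity analysis.
- Keep one-off website development excluded, and say that this is the only part of the exclusion that remains.
- Report maintenance and promotion alone as a labelled roll-out scenario, with the stated assumption that the effect is unchanged without support.

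The cost is a brief time log, one additional cost line and a somewhat less favourable ICER. Treatment, sample size and the primary outcome do not change.
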